## Methods/design

Because of the complexity of the problem (discomfort is the result of many factors that, for ethical and practical reasons, researchers cannot control) and the explorative nature of this study, it would be conceived as a multi-case study in which the setting and participants are deliberately chosen. The aim is not to achieve representativity, but rather to describe some typical cases which can provide maximum insight.

### Participants

In modal hospitals and modal homes for the elderly, forty patients will be selected. In each setting 20 participants will be included consecutively, which should result in 40 detailed case studies. Patients will be deliberately selected to gain maximum insight and reflect variability regarding medical conditions.

#### Inclusion criteria

Patients may be included if they are considered by their treating physician as:in their last week of lifein conditions that might, when not treated, cause high levels of distresspalliative sedation will be started

The treating physicians (specialists at the PCU/ICU or general practitioners at homes for the elderly) will be asked to determine whether or not the patients meet these conditions by means of a checklist on these 4 criteria. To optimally reflect daily practice, no further specific instructions will be given on how to evaluate these criteria and treatment will be according to the physician’s judgment and the best practice.

### Procedures

For this prospective study methods from social sciences (qualitative data collection based on interviews, observation), quantitative assessments (scales to assess awareness and discomfort) and neurophysiological data will be combined. Hence, a combination of methods that can be considered fairly objective (e.g. EEG and physiological parameters) and rather subjective methods (e.g. observations by family members) will be used to assess discomfort and awareness. Therefore, the following data will be collected:

*1. Assessment by caregivers* (physicians and nurses) in the routine manner. As explained above, this can be based either on their ‘experience’ or on tools they routinely use in their practice. Every day all treating physicians and nurses will be asked to fill in a brief questionnaire (3 VAS scales) on the patient’s level of awareness (no awareness- completely aware), comfort (no pain – very severe pain) and ability to communicate (no communication possible - full communication possible). After the patient has deceased, all caregivers will be interviewed and asked to comment on their assessments.

*2. Family members’ perception* of the quality of the dying process, their opinion about the patient’s comfort and awareness and their impression of whether they had any kind of (non-verbal) contact with the patient. Parallel with the above described procedure, family members will also be asked to fill in the same 3 VAS scales. Semi-structured interviews will be conducted before and after the patient has deceased.

*3. Assessment by 2 trained investigators* using 1 scale that is mentioned in the Flemish palliative sedation guideline and 3 other scales that have been proposed in the literature [16]:3.1CCPOT (Critical Care Pain Observational Tool), a tool specifically developed for use in patients with limited consciousness [8].3.2RASS (Richmond Agitation-Sedation Scale) [21].3.3M-ESAS (Modified Edmonton Symptom Assessment Scale, validated for a Flemish Palliative Care Population) [22].3.4BPS-NI (Behavioral Pain Scale Non-Intubated) [23].

*4. Neurophysiological assessments* of distress and level of awareness using fMRI has been successfully used to detect awareness and distress that could not be detected by thorough behavioral assessment [10, 13, 14, 24, 25]. Issues of availability and extra stress incurred by patients when transferred are making the use of fMRI for practical and ethical reasons not feasible.

EEG has recently been shown to provide a feasible and methodologically sound alternative for bedside detection of awareness and pain [26–28]. Although results from these methods need to be interpreted with caution, they can provide important indicators that are especially valuable for assessments in non-communicative patients. Data will be collected with a Neurosense monitor that can easily be used and set up. It displays two frontal EEG signals, and calculates a number of parameters including the bilateral WAVcns index (Wavelet Anesthetic Value for Central Nervous System), ranging from 100 (awake) to 0 (flat EEG). The lower the index, the lower the likelihood of consciousness. The recommended WAVcns for general anesthesia with low probability of consciousness is between 60 and 40. For technical details on the respective measurements of awareness and distress we refer to Schulz E et al. and Cruse D et al. [24, 29].

Additionally, heart rate variability (HRV) will be measured using an ANI monitor. HRV is the variation in time intervals between heartbeats and reflects the effect of the vagus nerve on the heart, which is inhibited during pain. It has already been widely studied in relationship to pain, and seems to be a promising biomarker [30]. However, studies with palliative sedated patients show contradicting results thus far [31, 32]. A promising non-invasive technique is the continuous monitoring of HRV transformed into an analgesia nociception index (ANI, 0–100), which assesses parasympathetic activity as a possible measure of nociception [33]. The ANI provides greater stability than raw indices of HRV. A recent study showed that ANI is effective in detecting pain in deeply sedated critically ill patients [34]. The analgesia nociception index is a non-invasive tool based on the analysis of the respiratory fluctuations of heart rate that mainly reflect the variability in the parasympathetic tone. The NeuroSense and ANI monitor record the EEG and ECG signal continuously, enabling a quantitative assessment of these parameters. The data can be used to assess the level of sedation but also to register negative and positive emotion-related activities such as the voice of loved ones and distress.

*5. Observation* of the patient to detect e.g. restlessness, movements etc. To assure a more precise and reliable observation, video and audio registrations will be made of the patient.

*6. Background information* based on the patient’s medical file, observation and interviews.6.1Characteristics of the patient (age, gender, profession…).6.2Medical information: history, medical condition, feeding, medication, etc.).6.3Pharmacological information (especially medication aimed to improve comfort e.g. sedatives, painkillers etc.)6.4Environmental information (e.g. the presence of next of kin, noises etc.)

Data will be collected every day, starting from the day when palliative sedation is initiated until the patient dies. Neurophysiological data will be collected continuously. Video and audio registrations will preferably take place non-stop (in consultation with the family) but may be interrupted during family visits to respect privacy.

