**Methods:**

In this study we will observe 40 patients starting with initiation of palliative sedation until death. Assessment of comfort based on behavioral observations will be related with the results from a NeuroSense monitor, an EEG-based monitor used for evaluation of the adequacy of anesthesia and sedation in the operating room and an ECG-based Analgesia Nociception Index (ANI) monitor, which informs about comfort or discomfort condition, based on the parasympathetic tone. An innovative and challenging aspect of this study is its qualitative approach; “objective” and “subjective” data will be linked to achieve a holistic understanding of the study topic. The following data will be collected: assessment of pain/comfort by the patients themselves (if possible) by scoring a Visual Analogue Scale (VAS); brain function monitoring; monitoring of parasympathetic tone; caregivers’ assessment (pain, awareness, communication); relatives’ perception of the quality of the dying process; assessment by 2 trained investigators using observational scales; video and audio registration.

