## Background

Once death is imminent, a major concern of family members and caregivers is to assure maximal comfort for the patient during this terminal phase. This can often be achieved by ‘conventional’ pharmacological drugs such as opiates or other symptom-controlling drugs. However, when symptoms are refractory or very severe, e.g. suffocation, a more drastic option may be chosen, known as palliative sedation, terminal sedation or continuous deep sedation (CDS). In such cases comfort is sought by reducing the patient’s level of consciousness [1]. Notwithstanding palliative sedation is ethically controversial, this practice has substantially increased in hospitals, nursing homes and in the home setting. The overall reported incidences vary between 8% and 17% of all deaths [2–5]. Although CDS is more often used in palliative care settings, it is also applied in other populations such as coma patients and the demented elderly.

It is assumed that patients who are sedated according to current standards of care and the guidelines of CDS are unaware of their clinical situation and therefore do not experience symptoms of discomfort such as dyspnea, delirium, and other distressing conditions that are common during the terminal phase. However, a critical evaluation based on more recent evidence raises the question whether the current assessments of suffering and awareness are accurate. Three kinds of problems (assessment of (dis)comfort, the notion of (un)awareness, and titration of drugs) can be discerned.

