##### Research questions

Are sedated non-communicative dying patients free of pain and other kinds of discomfort?Do the findings of the different assessment methods correspond to each other? In casu:The commonly used assessments (observational scales)The perceptions of family membersThe neurophysiological measurementsAre there differences according to the setting? In casu:Homes for the elderlyHospitals (with Palliative Care Units (PCU) and/or Intensive Care Units (ICU))What is the effect of contextual factors:Medical and pharmacological factors (diseases, medical condition, feeding, medication, etc.).Environmental factors (e.g. the presence of next of kin, noises etc.)

If one or more observational scales provide conclusive results that correspond to the results of the EEG and/or ANI measurement, this can be considered validation. In that case it would seem that observational scales can be reliably used in the palliative population. If not, then we may need to rethink our ways of measuring comfort in dying patients.

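### The daily comfort VAS is in fact a pain scale, so caregivers and relatives give no same-day score for discomfort other than pain

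*Protocol article*

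**What the plan says.** Procedures, item 1, asks all treating physicians and nurses to complete three VAS lines each day. Their descriptions are:

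- "awareness (no awareness- completely aware"
- "comfort (no pain – very severe pain"
- "ability to communicate (no communication possible - full communication possible"

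Item 2 extends this to relatives: "family members will also be asked to fill in the same 3 VAS scales".

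The first research question is "Are sedated non-communicative dying patients free of pain and other kinds of discomfort". The Background describes what sedation is meant to spare the patient as "symptoms of discomfort such as dyspnea, delirium, and other distressing conditions".

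The Abstract uses other names. It lists "caregivers’ assessment (pain, awareness, communication", so the caregiver item there is pain, and it describes the patient's own rating as "assessment of pain/comfort by the patients themselves (if possible) by scoring a Visual Analogue Scale (VAS", which merges the two terms.

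**The concern.** The study asks about discomfort in general, but the line that carries the word comfort can record only pain. The article itself separates the two: the section on how to improve assessments gives pain versus delirium as an example of distinguishing types of discomfort, and the Background gives suffocation as an example of a symptom severe enough to lead to sedation.

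What is at stake is the comparison between methods. The second research question asks whether observational scales, relatives' perceptions and neurophysiology agree. The Limitations section says the study relies on triangulating measures taken at the same moment. For non-pain discomfort, caregivers and relatives contribute no such measure. If their marks near the good end are reported as comfort, the study may conclude that patients were comfortable when the raters said only that they were free of pain. These patients cannot be rated again later.

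**Working it through.** The point turns on wording, so the check sets the instrument against the question.

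**Step 1: what each line can record.** Take four patients, each rated by someone who follows the printed anchors.

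| Patient as judged by the rater | Awareness line | Comfort line | Communication line |
|---|---|---|---|
| In severe pain | level of awareness | worst end | level of communication |
| No pain, severely breathless | level of awareness | best end | level of communication |
| No pain, delirious | level of awareness | best end | level of communication |
| No pain, no other discomfort | level of awareness | best end | level of communication |

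The last three rows receive the same comfort score. The first research question needs rows two and three to be told apart from row four.

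**Step 2: who else records it.** Item 3 gives the two trained investigators four scales, including the M-ESAS (by name a symptom scale) and the RASS (agitation and sedation). The article does not assign these to caregivers or relatives. Item 1 lets caregivers base their judgement on tools they routinely use, but does not list scores from those tools as study data. Caregivers are interviewed after the death, relatives before and after it. So the comfort line is the only daily quantitative comfort rating specified for these two groups.

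**Step 3: how many ratings are affected.** Sample size expects about 5 VAS scores per patient from relatives and more from staff; the Abstract gives 40 patients. 40 × 5 = 200 relatives' forms, plus a larger number from staff. The number of non-pain discomfort scores among them is 0.

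**Step 4: direction.** The awareness and communication lines run from none to full of the thing named. The comfort line runs from the best state to the worst, so a high mark means low comfort. The Procedures text on heart rate variability says vagal effect is inhibited during pain. The expected sign of an association with the ANI therefore depends on whether the line is read as comfort or as pain.

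**Step 5: does the plan's power figure bear on this?** Sample size states close to 80% power to show a correlation above 0.30 if the true value is 0.45. Fisher's z with n = 40 × 5 = 200 scores taken as independent (an assumption) gives:

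- (atanh 0.45 − atanh 0.30) × √197 = (0.4847 − 0.3095) × 14.04 = 2.459
- one-sided 5%: Φ(2.459 − 1.645) = 79.2%, which matches
- two-sided 5%: Φ(2.459 − 1.960) = 69.1%, which does not

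The figure can be reproduced, but it concerns WAVcns as a measure of sedation and does not say which VAS is meant. The sedation context points to the awareness line. It does not measure the effect of the comfort line's wording.

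**The case against.** The strongest reply is that the study is a qualitative multi-case design and the VAS is not these raters' only channel. Relatives are asked for their opinion on comfort and are interviewed before and after the death; caregivers are asked to comment on their assessments. The investigators' M-ESAS and RASS reach beyond pain, and video captures restlessness. This stands in part: it would be wrong to say that caregivers and relatives cannot report non-pain discomfort at all, or that the first research question rests on this VAS. But an interview is not a same-day score that can be set against a monitor reading or an M-ESAS entry, and caregivers' interviews come only after death.

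A reader might also infer that two of the three perspectives compared in the study are disabled. The Research questions section does not support that: it lists observational scales, family perceptions and neurophysiology, and caregivers are not named as one of the three.

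The most tempting stronger reading is that the label makes some raters mark the wrong end and so dilutes the correlations. If a share f of marks were reversed about the midpoint, with scores centred there, 0.45 would become 0.45 × (1 − 2f): 0.36 at f = 10% and 0.27 at f = 20%. The arithmetic is right, but nothing in the article supports any value of f. Both anchors are explicit pain descriptors, the form is not reproduced, and the Abstract calls the item pain, so raters may never see the word comfort. The 0.45 and 0.30 also come from the sedation calculation and are not tied to this line. No loss of correlation or power should be claimed.

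**Conclusion.** The concern holds as a mismatch between construct and instrument. The line called comfort measures pain, and for physicians, nurses and relatives it is the only daily comfort score the article specifies. On the planned numbers, about 200 relatives' forms and a larger number of staff forms would hold no quantitative information on breathlessness, delirium or other non-pain discomfort. This assumes that raters follow the anchors as printed in the article and that the planned counts are reached.

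The conflict between label and direction is present in the text and needs to be reconciled. Its practical effect is unknown. The interviews and the investigators' scales soften the consequence but do not supply the missing same-day score. The point does not depend on any correlation or power figure. The change should be made, since it is small and the ratings cannot be recovered afterwards.

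**What to change.** 1. Rename the existing line *pain*, keep its present anchors, and use that name in both the Abstract and Procedures.
2. Add one line for caregivers and relatives, running in the same direction: *discomfort of any kind*, from *completely comfortable* to *extreme discomfort*.
3. State the use of each: the pain line for comparison with the pain scales (CPOT, BPS-NI), and the discomfort line for the first research question and for same-day comparison with the M-ESAS and the monitors.
4. Analyse scores already collected as pain only, and draw no conclusion about overall comfort from them. Check the form in use first, to confirm that it carried the pain anchors.

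The cost is a reworded form, one extra VAS mark each time it is completed, and no discomfort score for patients already observed. If the form can no longer be changed, steps 1 and 4 still apply, and non-pain discomfort from these two groups should be reported from the interviews alone.

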### Sample size

A previous study learns that a correlation of 0.45 was found between Bispectral Index (BIS) monitoring and the Ramsay scale [35]. A similar correlation can be expected between the WAVcns and the VAS in the present study. However, in order to become a successful measure of sedation, we require the correlation between both measures to be significantly higher than 0.30. Although EEG monitoring would allow continuous data collection, the VAS will be completed only once or twice a day by relatives (more often by trained investigators) to keep burden as low as possible. As we expect patients can be monitored during 2–3 days on average, some 5 VAS scores (from relatives, more from staff) will be available per patient. This results in a close to 80% probability for our study to find a correlation higher than 0.30 if the actual correlation is 0.45.

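### The only numerical criterion appears to pool scores from the start of sedation to death, so the contrast between awake and sedated could meet it without any agreement in the non-communicative patients the study asks about

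*Protocol article*

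**What the plan says.** The first research question (Research questions) asks: "Are sedated non-communicative dying patients free of pain and other kinds of discomfort". The same section says that if observational scales correspond to the EEG and/or ANI results, this can count as validation and the scales could be relied on in the palliative population.

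Collection covers the whole course of sedation. The abstract says: "In this study we will observe 40 patients starting with initiation of palliative sedation until death". Procedures says: "Data will be collected every day, starting from the day when palliative sedation is initiated until the patient dies". Moments when the patient is still aware are foreseen. The abstract plans self-scoring by the patient where possible, and in Procedures both the awareness VAS and WAVcns extend to full wakefulness. Entry requires only that sedation is going to be started (Inclusion criteria).

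The one numerical criterion is in Sample size: "in order to become a successful measure of sedation, we require the correlation between both measures to be significantly higher than 0.30". The two measures are WAVcns and the VAS. That section expects about five VAS scores per patient over two to three days, and states power of nearly 80% if the true correlation is 0.45.

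Inclusion criteria lists three conditions and then has the physician confirm them "by means of a checklist on these 4 criteria".

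**The concern.** A correlation over a wide range of states can be produced by the difference between the states alone. A score taken before sedation has taken effect tends to be high on both WAVcns and the awareness VAS. Later scores tend to be low on both. The pooled correlation then shows that observers and monitor can both tell an awake patient from a sedated one. That says little about whether they agree once the patient is unresponsive.

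Agreement in the unresponsive patient is what the Background is about: observers may miss residual awareness or distress in patients who look unconscious. Monitoring is expected to last only two to three days, so the day of initiation may supply a sizeable share of all scores. If the pooled correlation met its criterion and were read as the validation described in Research questions, it could support a conclusion about non-communicative patients that the data do not contain.

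**Working it through.** **Inputs from the protocol.** 40 patients; about 5 VAS scores each, so 40 × 5 = 200 pairs; threshold 0.30; assumed true correlation 0.45, carried over from an earlier comparison ("A previous study learns that a correlation of 0.45 was found between Bispectral Index (BIS) monitoring and the Ramsay scale"); power close to 80%.

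**Inputs not given, therefore assumed.** Alpha 0.05, one-sided unless stated; share *p* of scores taken while awake, 5% to 20%; separation *d* between awake and sedated on both measures, 1 to 4 within-state SDs.

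**1. Reproducing the power.** Fisher z for one correlation, pairs treated as independent:

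power = Φ[(atanh 0.45 − atanh 0.30) × √(n − 3) − z]

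- n = 200, one-sided: (0.4847 − 0.3095) × √197 − 1.645 ≈ 0.81, so power is 79.2%.
- n = 200, two-sided: 69.1%. Two-sided power is 76.9% at 240 pairs and 83.0% at 280.
- n = 100, one-sided: 53.2%. n = 40, one-sided: 28.1%.

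The stated figure thus needs about 200 pairs or more, which means counting all the scores in the window.

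**2. The bar actually set.** The correlation must be significantly above 0.30, which is more than an observed value above 0.30. At n = 200, one-sided:

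r = tanh(atanh 0.30 + 1.645/√197) = tanh(0.4267) ≈ 0.403

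**3. Pooled correlation with zero agreement within each state.** For a two-state mixture with equal separation *d* on both measures:

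r = p(1 − p)d² / [1 + p(1 − p)d²]

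| p | d = 1 | d = 1.5 | d = 2 | d = 2.5 | d = 3 | d = 4 |
|---|---|---|---|---|---|---|
| 0.20 | 0.14 | 0.27 | 0.39 | 0.50 | 0.59 | 0.72 |
| 0.10 | 0.08 | 0.17 | 0.27 | 0.36 | 0.45 | 0.59 |
| 0.05 | 0.05 | 0.10 | 0.16 | 0.23 | 0.30 | 0.43 |

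Solving for *d* at r = 0.4025: d = √{[0.4025/0.5975] / [p(1 − p)]}.

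- p = 0.20: √(0.6736/0.16) ≈ 2.05
- p = 0.10: √(0.6736/0.09) ≈ 2.74
- p = 0.05: √(0.6736/0.0475) ≈ 3.77

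**4. Chance of meeting the criterion.** Simulation of 40 patients × 5 scores, with no agreement in either state:

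- p = 0.20: 1% at d = 1.5, 42% at d = 2, 98% at d = 2.5.
- p = 0.10: 1.5% at d = 2, 28% at d = 2.5, 76% at d = 3.
- p = 0.05: 0.9% at d = 2.5, 9% at d = 3, 64% at d = 4.

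Restricted to the sedated scores of the same simulated studies, the observed correlation exceeded even 0.30 in under 0.5% of runs.

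**5. Is such a separation conceivable?** Procedures puts awake at 100 and the range recommended for general anesthesia at 40 to 60, a gap of 40 to 60 points. With an assumed within-state SD of 10 to 20 points, this is 40/20 = 2 to 60/10 = 6 SDs on WAVcns. The document offers no comparable figure for the VAS.

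**The case against.** The strongest reply is that the protocol nowhere defines the analysis set. The Procedures sentence is a collection rule, Sample size merely counts scores, and a condensed article may leave restriction by state to an analysis plan that is not shown. This stands in part: pooling is inferred, not stated. But the power figure depends on all the scores, and the mismatch between that criterion and the research question lies in this document.

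Second, the criterion is set for a measure of sedation. For that purpose the change from awake to sedated is partly real signal, and detecting changes in awareness is a stated aim. This stands. It is the reason to keep both the window and the overall correlation.

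Third, the size rests on assumptions. No share of awake scores is given, and scoring from the day of initiation does not prove that any score precedes the effect of sedation. The 40 to 60 points are general-anesthesia values, whereas the Background calls for sedation no deeper than needed, so the true gap may be smaller. Sample size also does not say which of the three VAS scales is meant; awareness is only the natural reading. All of this stands.

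A reader might go further and infer that the study will wrongly declare patients free of pain. The document does not support this. The correlation does not decide that question, and the design draws on ANI, video, interviews and four scales in exploratory case studies. Nor does the count of three criteria against four show that a requirement of non-communication was dropped. Patients enter before sedation starts and may consent themselves, and the list may have been damaged in text extraction.

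**Conclusion.** The concern holds in limited form. The sole numerical criterion appears to pool all scores from initiation to death, while the question and the validation inference concern non-communicative patients. With no agreement in either state, the pooled correlation can still clear the bar of about 0.403 when about 20% of scores are taken awake and both measures differ by roughly 2.05 SDs or more, or about 2.74 SDs at 10%. This assumes independent pairs, one-sided alpha 0.05, equal separation on both measures and the awareness VAS.

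It is a possibility, not a prediction. With separations of 1.5 SDs or less at these shares, or 5% awake scores and anything short of nearly 4 SDs, the contrast alone would rarely suffice. It would be too strong to say that an observed correlation just above 0.30 meets the criterion, or that the collection window is wrong.

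**What to change.** - Keep the collection window and the all-assessment correlation, and label the latter as answering how well WAVcns measures sedation. State which VAS is used.
- Pre-specify a second WAVcns–VAS correlation, restricted to assessments at which the patient is non-communicative. Define that state in advance by a stated cut-off on the communication VAS or RASS, both already collected. If RASS defines the state, it should not also be validated within it. If the communication VAS does, it is better taken from a different rater than the one whose score is correlated.
- In Research questions, base any validation statement for non-communicative patients on the within-state result.
- State its lower precision. If one score in five drops out, 160 pairs remain, and on the same Fisher z basis power is Φ(0.1752 × √157 − 1.645) = Φ(0.55) ≈ 71%, against 79.2% for 200. This assumes that 0.45 still holds; a restricted range may lower it.
- Separately, as a minor wording point that does not bear on the above, reconcile the three listed inclusion criteria with the stated four.

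No new data are needed. The cost is some added analysis text, fewer scores and a wider interval for the restricted correlation.
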